### Control group: oral naproxen sodium therapy

Naproxen sodium was administered for migraine prophylaxis during each menstrual cycle, for 3 consecutive cycles (consistent with the experimental group).

Timing: Initiated 2–3 days before the expected onset of menstruation, and continued until menstruation ended (typically 5–7 consecutive days per cycle).

Dosage: Oral naproxen sodium tablets, 550 mg, twice daily (after breakfast and dinner).

Cycle schedule: Repeated for 3 complete menstrual cycles, aligned with the intervention phases of the press-needle group.

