**Methods:**

This is a randomized, active-controlled, parallel-group trial. A total of 76 eligible women aged 18–45 years with migraine without aura and diagnosed with pure menstrual migraine or menstrually-related migraine will be recruited and randomly allocated to receive either sequential press-needle therapy or oral naproxen sodium therapy. In the press-needle group, treatment is delivered at designated acupoints across two phases (pre-menstrual and post-menstrual) per menstrual cycle. Each phase includes 2 sessions with a 2-day interval (4 sessions per cycle), repeated for 3 consecutive cycles. In the control group, oral naproxen sodium (550 mg twice daily after breakfast and dinner) is initiated 2–3 days before the expected onset of menstruation and continued until menstruation ends (5–7 consecutive days per cycle), also for 3 complete cycles. Compliance is monitored by a daily medication diary and telephone follow-up. The primary outcome is the change in the number of headache days with a peak pain intensity of ≥4 (moderate-to-severe) on a 0–10 Numeric Rating Scale (NRS, where 4–6 = moderate, 7–10 = severe) per menstrual cycle from baseline to the end of the 3-month intervention. Secondary outcomes include headache intensity, functional impact, quality of life, acute medication use, and heart rate variability indices. Exploratory outcomes include serum biomarkers and resting-state functional MRI.

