### Eligibility criteria

#### Inclusion criteria

Meets the diagnostic criteria for “migraine without aura” (ICHD-3 code 1.1)” as defined in the International Classification of Headache Disorders, 3rd Edition (ICHD-3);Meets the diagnostic criteria for “pure menstrual migraine” (A1.1.1) or “menstrually-related migraine” (A1.1.2) as outlined in the appendix to the ICHD-3, and this diagnosis has been validated by a prospective headache diary covering three consecutive menstrual cycles;Age 18–45 years, with a normal menstrual cycle of 28 ± 7 days and a menstrual duration of 3–7 days;During the 3-cycle screening period, at least 2 of the 3 menstrual cycles have 2–14 days with moderate-to-severe headache (NRS ≥ 4) per cycle (meeting the ICHD-3 appendix criterion for PMM or MRM). Baseline data for the primary outcome will be calculated as the average number of moderate-to-severe headache days across all qualified cycles (i.e., those cycles meeting the 2–14 day criterion) during the screening period;Complete the daily headache diary throughout the 3-cycle screening period (with a completion rate of ≥80% for daily entries within each menstrual cycle) to demonstrate good patient compliance;Voluntary signing of the informed consent form.

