#### Exclusion criteria

Primary diagnosis of other primary or secondary headache disorders (e.g., tension-type headache, cluster headache, migraine with aura, medication-overuse headache);Concurrent severe or unstable cardiovascular, cerebrovascular, hepatic, renal, or hematopoietic system diseases, or malignant tumors;Diagnosed with severe mental disorders such as major depressive disorder, anxiety disorder, or bipolar disorder;Currently pregnant, breastfeeding, or planning to become pregnant within the next 6 months;Use of hormonal contraceptives or other hormonal therapies affecting the menstrual cycle within the past 3 months; regular use of pain relievers, triptans, or ergotamine-based acute migraine medications for ≥10 days per month within the past 3 months; or receipt of migraine preventive medications, acupuncture, or other systemic non-pharmacological treatments within the past month;Presence of coagulation disorders, severe osteoporosis, or skin infection/lesions at the proposed acupuncture site; history of allergy or severe adverse reactions to acupuncture or press-needle therapy;Currently participating in other interventional clinical trials;Allergy to naproxen sodium or other NSAIDs; history of active gastrointestinal ulcers or gastrointestinal bleeding; or severe hepatic or renal insufficiency;Other conditions deemed by the investigator to preclude participation in the trial or pose significant safety risks.

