#### Criteria for discontinuation of intervention

Occurrence of a serious adverse event (SAE) related to the study intervention;Confirmed pregnancy during the trial;Significant worsening of headache requiring emergency treatment or alternative therapy, as determined by the investigator;Voluntary withdrawal of consent by the participant;Lost to follow-up, with no contact possible for assessments or interventions;Major protocol violation (e.g., use of prohibited medications, non-adherence to intervention, compromising efficacy or safety evaluation);Development of a new medical condition contraindicating continued trial participation.

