### Prohibited (from screening to final follow-up)

New migraine prophylactic drugs (beta-blockers, anticonvulsants, antidepressants, CGRP monoclonal antibodies) any acupuncture, press-needle, moxibustion, cupping, tuina, or Chinese herbal medicine for headache/menstrual disorders (except the assigned study intervention) new hormonal therapy or procedures altering menstrual cyclicity participation in other interventional clinical trials any other interventions interfering with study outcomes or safety.

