### Safety outcomes

All adverse events (AEs) and serious adverse events (SAEs) were recorded from the time of signed informed consent until the 3-month follow-up after intervention. The occurrence time, symptoms, severity, duration, management, outcome, and causality with interventions were documented in detail.

Sequential press-needle group: Local skin reactions at the press-needle insertion sites were mainly monitored, including redness, itching, pain, rash, infection, and bleeding.

Oral naproxen sodium group: Adverse reactions related to NSAIDs were intensively monitored, including gastrointestinal reactions (nausea, stomachache, acid reflux, abdominal distension, gastrointestinal discomfort), neurological reactions (dizziness, headache, fatigue), skin allergy (rash, itching), and abnormal liver and renal function.

All systemic AEs were recorded in both groups. The incidence, severity, and causality of AEs were compared between groups to comprehensively evaluate the safety of the interventions.

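### The naproxen rule gives 5–10 on-time dosing days rather than 5–7, and sets no limit when menses are late or do not come

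*Protocol article*

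**What the plan says.** The control-arm section of the protocol article fixes the timing of each naproxen course: "Initiated 2–3 days before the expected onset of menstruation, and continued until menstruation ended (typically 5–7 consecutive days per cycle". The dose is 550 mg twice daily, repeated for three cycles. The Methods paragraph of the abstract gives the same rule but drops the word *typically*: the drug "is initiated 2–3 days before the expected onset of menstruation and continued until menstruation ends (5–7 consecutive days per cycle".

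The inclusion criteria admit women "with a normal menstrual cycle of 28 ± 7 days and a menstrual duration of 3–7 days".

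On pregnancy, the exclusion criteria bar women who are "Currently pregnant, breastfeeding, or planning to become pregnant within the next 6 months". They also bar "Use of hormonal contraceptives or other hormonal therapies affecting the menstrual cycle within the past 3 months", and the list of prohibited care adds "new hormonal therapy or procedures altering menstrual cyclicity". The criteria for discontinuing the intervention include "Confirmed pregnancy during the trial".

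Under Compliance monitoring, telephone follow-up checks timing and dosage. Under Safety outcomes, the naproxen arm is watched closely: "Adverse reactions related to NSAIDs were intensively monitored, including gastrointestinal reactions".

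**The concern.** A course begins on a predicted date and ends on an observed event. Two things follow.

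First, the course length depends on how long the woman bleeds, and the eligible bleeds run past what 5–7 days can hold. For a woman with a 7-day bleed, the abstract's two statements conflict. Stopping on day 7 respects the stated length but not the stop rule, and dosing to day 9 or 10 does the reverse. Staff asked to verify correct timing have no single answer.

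Second, the rule is open-ended. Every day that menses are late is a further day at 1.1 g, and if menses do not come, the event that ends the course does not happen. Unplanned pregnancy remains possible in this population. Women planning pregnancy are excluded and non-hormonal contraception is open to participants, but recent users of hormonal contraceptives are excluded and new hormonal therapy is prohibited. Followed literally, the rule makes NSAID exposure longest when a period is late, which is when pregnancy should be considered. Nothing in the dosing rule makes a late period a prompt to hold the drug or to test, so the pregnancy stop waits for a confirmation that the rule does not trigger.

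**Working it through.** **Inputs.** Lead of 2 or 3 days before expected menses (control-arm section); bleed of 3 to 7 days (inclusion criteria); dose 2 × 550 mg = 1.1 g per day and three courses (control-arm section). L is the number of days menses are late. The documents give no distribution for L, so the values below are illustrations.

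**Formula.** Dosing days = lead + L + bleed, with the last bleed day dosed.

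**Reproducing the stated 5–7 days (L = 0).**

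| Bleed (days) | Lead 2 | Lead 3 |
|---|---|---|
| 3 | 5 | 6 |
| 4 | 6 | 7 |
| 5 | 7 | 8 |
| 6 | 8 | 9 |
| 7 | 9 | 10 |

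The lower end, 5, reproduces. The upper end does not: the rule gives 10. A length of 5–7 days fits bleeds of 3–4 days, and of 5 days only with a 2-day lead. Five of the 10 whole-day combinations exceed 7 days. If the last bleed day is not dosed, the range is 4–9 days, which still exceeds 7.

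**Dose, on-time menses.**
- Per course: 5 × 1.1 = 5.5 g to 10 × 1.1 = 11.0 g, against 5.5 g to 7 × 1.1 = 7.7 g as stated.
- Over three cycles: 15–30 days (16.5–33.0 g), against 15–21 days (16.5–23.1 g). The upper ends assume the longest course in all three cycles.

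**Menses not on time, rule as written.**
- 1 day early: 4–9 days.
- 1 day late: 6–11 days.
- 2 days late: 7–12 days.
- 3 days late: 8–13 days.
- 7 days late: 12–17 days.
- Menses absent: no end point from the course rule.

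**Effect of a 10-day cap.** Combinations shortened: 0 of 10 on time, 1 of 10 at 1 day late, 3 of 10 at 2 days, 5 of 10 at 3 days.

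**Effect of holding after expected date + 3.** With no menses by then, dosing has run lead + 4 = 6–7 days (6.6–7.7 g), which leaves 3–4 days within the cap. The Introduction defines the perimenstrual window from the second day before to the third day after menstruation. Taking the third day as counted from onset, the window has five days: −2, −1, +1, +2, +3.

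| Days late | Window days dosed, no resumption | With resumption at onset, within 10 days |
|---|---|---|
| 0–3 | 5 of 5 (no hold occurs) | 5 of 5 |
| 4 | 2 of 5 | 5 of 5 |
| 5 | 1 of 5 | 4 of 5 |
| 6 or more | 0 of 5 | 3 of 5 |

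The resumption column assumes that the negative test is in hand by onset.

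**The case against.** The strongest reply has four parts.

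- **The operative section says *typically*.** A typical length is not a range for every eligible woman, and occasional 8–10 day courses do not contradict it. This stands for the control-arm section. It does not stand for the abstract, which has no qualifier, and it does not supply a limit.
- **An article condenses the full protocol.** Pregnancy testing or a maximum drug supply may be set out in a document not shown. This stands for the test procedure, so its absence here is not itself the finding. But the article prints a complete start rule and stop rule, and that stop rule has no end when menses do not come.
- **There are mitigations.** Initial screening covers cycle regularity, the three-cycle diary (Recruitment process) improves the predicted date, telephone follow-up checks timing and dosage, and early menses shorten courses. These lower the risk. None states what to do when a period is late, and the start date remains an estimate.
- **Stopping early could weaken the comparator.** This stands. Without resumption, menses 6 or more days late would leave the whole perimenstrual window undosed in the control arm, which could favour press-needle therapy. Resumption after a negative test must therefore be required.

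A reader might also infer that courses of 8–10 days are unsafe. The documents do not show this, and the proposed cap itself accepts 10 days.

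**Conclusion.** The point holds as a minor-to-moderate safety correction. With on-time menses the written rule gives 5–10 dosing days per course, up to 3 days and 3.3 g (11.0 − 7.7) beyond the stated upper end. With late menses it adds 1.1 g per day with no stated maximum. With absent menses the per-course stop is never reached, and the pregnancy criterion needs confirmation. The arithmetic assumes whole days and dosing through the last bleed day.

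Two stronger readings are not supported. Five of 10 combinations above 7 days does not mean that half of the women exceed 7 days: the documents give no distribution of bleed length or lead, nor any frequency of late menses. Nor is the trial without pregnancy safeguards: it excludes pregnant women and those planning pregnancy, and it stops treatment on confirmation. The gap is that a late period triggers neither a hold nor a test in the dosing rule. The effect on trial outcomes is small.

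**What to change.** In the control-arm section and the abstract:

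1. Give the course as 5–10 days. The figure 5–7 may stay if it is marked as typical in both places.
2. State the stop as *until menstruation ends or a maximum of 10 dosing days, whichever comes first*.
3. Add: *if menses have not begun within [prespecified number, for example 3] days after the expected date, dosing is held and a urine pregnancy test is done; after a negative test, dosing resumes at the onset of menses within the same 10-day total.*

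The 10-day cap follows from the longest on-time course. The 3-day trigger is a suggestion, and the investigators should choose and fix their own value.

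Cost: a few sentences, an inexpensive urine strip for women with late menses, and a brief instruction to participants and to the staff who make the telephone checks. Sample size and on-time courses are unchanged. The downside is that some courses with late menses become shorter (the 1, 3 and 5 of 10 combinations above), and menses 5 or more days late lose one or two of the five window days even with resumption.

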### Compliance monitoring

Medication intake was recorded daily in a medication diary. Adherence was verified via telephone follow-up to ensure correct timing and dosage.

### Quality control

Practitioner Qualifications, Training, and Standardization.

The sequential press-needle intervention will be performed by licensed acupuncturists with at least 10 years of clinical experience.

The naproxen sodium intervention will be dispensed and managed by licensed pharmacists or registered nurses.

All study personnel will complete standardized protocol training before trial initiation, covering intervention procedures, outcome assessment, data recording, and adverse event management. Refresher training will be conducted regularly to ensure consistency.

### Blinding design

This is an open-label trial. Participants and intervention providers will be aware of the group assignments. To avoid detection bias, outcome assessors and statisticians will remain completely unaware of the group assignments throughout the trial. The following measures will be taken to maintain blinding:(1) Blinded outcome assessors: All outcome assessments will be conducted by trained assessors who were not involved in randomization or treatment administration. Participants will be instructed not to disclose their treatment group to the assessors during any assessment visit;(2) Blinded statisticians: Randomization codes will not be disclosed to the statisticians until the final data lock-in and completion of all pre-specified analyses. The dataset provided to the statistician will include coded treatment indicators (e.g., Group A and Group B) but will not reveal the correspondence to the actual interventions;(3) Data manager blinding: Data managers will use coded group identifiers to process and clean the data. They will not have access to randomization information.

To evaluate the influence of the open-label design, participants’ treatment credibility and expectancy will be assessed at baseline and explored as potential confounders in the analysis of treatment effects.

### Treatment fidelity and environmental control

Treatment fidelity will be verified by random audit and standardized record review:

For the press-needle group: documentation of acupoint location, needle retention time, and immediate adverse events.

For the naproxen sodium group: verification of drug dosage, administration timing, and participant adherence. All procedures will be conducted in a quiet, dedicated, and consistent clinical environment to minimize external interference.

### Relevant concomitant care: permitted and prohibited

### Permitted

Rescue medication: Paracetamol (acetaminophen) is allowed as the sole rescue medication for severe migraine attacks. Paracetamol was selected because (1) it has a distinct mechanism of action (central COX-2 inhibition) that does not interfere with the pharmacological effects of the prophylactic NSAID (naproxen sodium, a peripheral COX-1/COX-2 inhibitor); (2) it carries a significantly lower risk of medication-overuse headache (MOH) compared to triptans or combined analgesics (14), which is critical for maintaining the integrity of the primary outcome (headache frequency) over the 3-month intervention period; and (3) it is the most commonly used rescue analgesic in Chinese clinical practice with an established safety profile (15). NSAIDs (including naproxen sodium, except for the assigned prophylactic regimen), triptans, and ergotamines are strictly prohibited to avoid intervention overlap and medication overuse. All rescue medication use (dose and frequency) must be recorded in the daily headache diary, and participants will be instructed to limit paracetamol use to a maximum of 2 days per week to minimize the risk of analgesic overuse.

Non-pharmacological care: Only general lifestyle advice (hydration, sleep, stress management, diet) is permitted; no headache/menstrual-specific non-drug interventions (e.g., acupuncture, moxibustion, herbal medicine) are allowed.

### Prohibited (from screening to final follow-up)

New migraine prophylactic drugs (beta-blockers, anticonvulsants, antidepressants, CGRP monoclonal antibodies) any acupuncture, press-needle, moxibustion, cupping, tuina, or Chinese herbal medicine for headache/menstrual disorders (except the assigned study intervention) new hormonal therapy or procedures altering menstrual cyclicity participation in other interventional clinical trials any other interventions interfering with study outcomes or safety.

### Outcomes

The timeline for evaluating research outcomes at each stage is detailed in Table 2.

**Table 2 tab2:** Schedule of outcome assessments across study time points.

Timepoint	Item				
	Baseline	Treatment period			Follow-up period
		1 month	2 months	3 months	3 months post-treatment
Enrollment					
Screening for eligibility	√				
Informed consent	√				
Randomization	√				
Intervention					
Press-needle therapy					
Sham press-needle therapy					
Assessment					
Primary outcome					
Headache days (e-diary)	√	√	√	√	√
Secondary outcome					
Headache intensity (NRS, e-diary)	√	√	√	√	√
MMFIQ	√	√	√	√	√
MSQ v2.1	√	√	√	√	√
Acute medication use (e-diary)	√	√	√	√	√
HRV recording	√	√	√	√	√
Exploratory outcomes					
Blood biomarkers (CGRP, E2, P4)	√	√	√	√	
Neuroimaging (subset, MRI)	√	√	√	√	
Other measures					
Blinding assessment		√	√	√	√
CEQ	√				
Adverse events monitoring		√	√	√	√
Protocol compliance check		√	√	√	
Concomitant medication review	√	√	√	√	√

NRS, Numeric Rating Scale; MMFIQ, Menstrual Migraine Functional Impact Questionnaire; MSQ, Migraine-Specific Quality of Life Questionnaire; HRV, Heart Rate Variability; CGRP, Calcitonin Gene-Related Peptide; E2, Estradiol; P4, Progesterone. CEQ, Credibility/Expectancy Questionnaire.

### Primary outcome

The primary outcome measure is the change in headache frequency, defined as:

Measurement: The mean change in the number of moderate-to-severe headache days per menstrual cycle from baseline (defined as the average across all qualified cycles during the 3-cycle screening period) to the end of the 3-month intervention period. Definition: A headache day is defined as any calendar day on which the participant experiences a headache meeting ICHD-3 criteria for migraine without aura (ICHD-3 code 1.1) with a peak pain intensity of ≥4 on the 0–10 Numeric Rating Scale (NRS, where 0 = no pain, 1–3 = mild, 4–6 = moderate, and 7–10 = severe; thus an NRS score of ≥4 captures both moderate and severe intensity levels). Data Source: Prospectively captured using a validated, electronic daily headache diary.

### Secondary outcomes

Secondary outcomes will evaluate headache burden, functional impact, acute medication utilization, and autonomic nervous system function.

#### Headache intensity

Measurement: Change in the average peak pain intensity of menstrual migraine attacks per menstrual cycle.

Tool: 11-point Numeric Rating Scale (NRS), where 0 = “no pain” and 10 = “worst pain imaginable.” Participants will rate peak pain intensity for each migraine attack in the ePRO system-integrated daily headache diary.

Assessment Timepoints: Baseline, Treatment Months 1–3, and 3-month post-treatment follow-up.

Analysis: Mean NRS score per menstrual cycle will be calculated, and between-group changes from baseline will be analyzed.

#### Headache-related functional impairment

Measurement: Change in functional disability specifically attributable to menstrual migraine.

Tool: Validated 7-item Menstrual Migraine Functional Impact Questionnaire (MMFIQ), scored 0–100 (higher scores indicate greater functional impairment).

Assessment Timepoints: Baseline, Treatment Months 1–3, and 3-month post-treatment follow-up.

Analysis: Between-group differences in absolute changes in MMFIQ scores from baseline will be compared.

#### Migraine-specific quality of life

Measurement: Change in disease-specific health-related quality of life.

Tool: Chinese version of the Migraine-Specific Quality of Life Questionnaire version 2.1 (MSQ v2.1), comprising three domains: Role Function-Restrictive (RR), Role Function-Preventive (RP), and Emotional Function (EF). Scores are transformed to a 0–100 scale (higher scores indicate better quality of life).

Assessment Timepoints: Baseline, Treatment Months 1–3, and 3-month post-treatment follow-up.

Analysis: Domain-specific and total scores will be computed, with between-group changes from baseline analyzed.

